As a second aim of the current work, we intend to contribute to filling the gap on the efficacy of ACT as a transdiagnostic approach to adolescents' SAD and GAD and amplify the transdiagnostic application of ACT to adolescents presenting these disorders (Study III). To do so, we will adapt, implement, and investigate the efficacy of an ACT Intervention to adolescents presenting SAD or GAD by exploring:Changes in primary (i.e., anxiety symptoms) and secondary (i.e., flourishing and PI/PF processes) outcomes following intervention. In view of the scarce but promising research on ACT efficacy in adolescents’ SAD [60, 74, 75], and GAD [60], improvements are expected at post-intervention for the two intervention groups (i.e., SAD and GAD), in comparison with a control group.The stability of change over time (i.e., 3 and 6 months after intervention completion). We expect improvements in the two intervention groups to be maintained.The equivalence of the efficacy of the same intervention delivered to the two intervention groups (i.e., SAD and GAD). Even though this aim has not yet been addressed, considering ACT conceptual and therapeutic transdiagnostic premises, similar effects on outcome measures are expected for both clinical groups.Mechanisms of change following the intervention in both intervention groups. Based on research conducted with adults on PI/PF processes as mechanisms of change following ACT [43], we expect similar effects in both intervention groups, with changes in PI/PF predicting changes in primary (i.e., anxiety symptoms) and secondary (i.e., flourishing) outcome variables. Specifically, we expect increases in PF processes and decreases in PI processes to promote lesser anxiety and greater flourishing. Given the lack of research on the role of each PI/PF process in producing changes in anxiety for adolescents’ GAD and SAD and the ACT assumptions that all processes are intertwined in their contribution to human suffering / flourishing [38], there were no grounds to define specific hypothesis regarding the differential role of each PI/PF process in contributing to decreases in anxiety and increases in flourishing between the two samples of adolescents, and so no specific and process-based hypotheses are put forward.

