### Study design and randomization of participants

The two aims of this research will be accomplished through diverse study designs. To accomplish the first aim, cross-sectional data will be collected from adolescents within a community sample, two clinical groups (with SAD or GAD), and a mentally healthy sample. For the second aim, a Randomized Controlled Trial (RCT) with a parallel design, 3 groups (i.e., Control Group, SAD Intervention Group, and GAD Intervention Group) and 4 assessment moments will be conducted following the CONSORT (Consolidated Standards of Reporting Trials) guidelines [77]. Adolescents from each clinical group from Study II will be randomly allocated (computer-generated random allocation,2:1 allocation ratio) to one of the intervention groups or to the control group. The two clinical intervention groups will receive the same intervention and will be assessed at pre- and post-intervention, and at 3- and 6- month follow-up using a set of self-report measures (see measures section). Adolescents from the control group will be assessed with the same set of self-report measures at 2 different time points (12 weeks interval), mimicking the pre- and post-intervention assessment moments. Given the high stability of both SAD and GAD, we consider ethical obligations to be imperative in not depriving these adolescents of intervention during follow-up assessments. As such, they will be assessed with a clinical structured interview (Mini-Kid; [78]) after the second time point and referred to the school psychology services if the difficulties persist. A flowchart of the study design is presented in Fig. 1.

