### Data analysis

IBM SPSS Statistics 25 will be used to conduct descriptive analysis. In study I, network analysis will be performed and visualized using R (Version 4.1.3). Network nodes will represent the scores for each PI/PF subscales and total scores for anxiety and flourishing measures. Edges will represent the weight of the correlations between the individual nodes. Centrality metrics (e.g., degree of centrality) will also be computed to investigate how important and influential each node is in the network. In study II, Mplus will be used to investigate the adjustment of a path analysis linking PI/PF processes to anxiety and flourishing, based on overall, comparative and residual based fit-indices. The moderator effect of groups (clinical SAD, clinical GAD and healthy adolescents) in those pathways will be estimated, testing for equality of pathways and means. In Study III, the IBM SPSS Statistics 25 will be used to explore treatment effects using Mixed ANOVAs and considering assessment moments as the within-subject and groups (SAD and GAD receiving intervention and Control Groups) as the between-subject effect; interaction effects will also be considered. Additionally, Mplus will be used to examine mechanisms of change after the intervention by performing two-wave latent change score models. These models allow to explore not only if significant changes emerged across assessment moments, but also to investigate the impact of changes in PI/PF constructs on changes in anxiety or flourishing. All Study III analyses will be carried out according to an intention-to-treat principle as suggested by the CONSORT guidelines [77]. Therefore, all participants randomized will be included in the statistical analyses and analyzed according to the group they were assigned regardless of having received/completed or not the intended intervention. Efforts will be made to obtain outcome data for all participants, even if they do not complete the intervention. If data is missing (e.g., participant refused to provide data, participant was unreachable, etc.) the last observation carried forward method will be employed.

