Finally, to the best of the authors' knowledge, this project will be the first to explore mechanisms of change following an ACT intervention for adolescents with SAD and GAD. We will consider all PI/PF processes, providing a more comprehensive examination of potential change mechanisms. This finding will further support the theoretical consistency of the ACT model and shed light on the processes responsible for change, thereby expanding the reach and benefits of ACT interventions. Based on previous research on the relevance of the ACT processes [43, 44] and on the transdiagnostic model underlying ACT (e.g., [37, 38]), we expect changes to those processes to predict changes in flourishing and anxiety symptoms similarly in both clinical intervention groups. From an ACT perspective ([39, 38]), adaptative behavioral change results from reducing inflexible patterns in which private events heavily influence action taking, distancing individuals from a valued living (PI) through cultivating the ability to fully contact the present moment as it is and persist in and/or change behavior in ways that bring meaning and vitality to one’s life (PF). Therefore, we expect decreases in PI processes and increases in PF processes to account for higher levels of flourishing and lower levels of anxiety following the intervention. This expectation aligns with the clinical features of many anxiety disorders, such as GAD and SAD, where avoidance of anxiety-triggering situations and rumination about future events are key maintenance factors encompassed within PI processes such as inaction, impulsivity, or avoidant persistence, and dominance of the conceptualized past/feared future. About specific PI/PF process, equal importance is attributed to them within the ACT framework, as the inflexible/flexible patterns of responding to internal experiences and contextual cues and engaging in unworkable/workable behaviors result from the interdependent interactions among them that sustain overall PI/PF ([38]). For instance, helping adolescents see their thoughts as mental events rather than literal representations of reality (cognitive defusion), may help foster present moment awareness which, in turn, creates space for them to choose to avoid less anxiety triggering situations and take more contextual useful and values guided actions [96]. At the empirical level, it remains unclear the extent to which each individual PF/PI process may be more or less important to promote change, particularly while accounting for all model processes (see [43] for a review). Thus, we did not make specific predictions about which PI/PF processes would most influence change in anxiety or flourishing, as all processes are expected to contribute to change.

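### Two-wave change-on-change models can show that PI/PF and outcome changes go together, but not that PI/PF change drives outcome change, as the plan reads them

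*Protocol article*

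**What the plan says.** The Aims section lists, as the fourth question of Study III, "Mechanisms of change following the intervention in both intervention groups". It expects similar effects in both groups, "with changes in PI/PF predicting changes in primary (i.e., anxiety symptoms) and secondary (i.e., flourishing) outcome variables", and adds the directional statement that "we expect increases in PF processes and decreases in PI processes to promote lesser anxiety and greater flourishing".

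For this aim the Data analysis section says that "Mplus will be used to examine mechanisms of change after the intervention by performing two-wave latent change score models". One stated use of the models is "to investigate the impact of changes in PI/PF constructs on changes in anxiety or flourishing". It does not name the two waves. The Discussion expects the result to "shed light on the processes responsible for change".

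Under Study design and randomization of participants, the intervention groups "will be assessed at pre- and post-intervention, and at 3- and 6- month follow-up". Controls complete the same measures "at 2 different time points (12 weeks interval), mimicking the pre- and post-intervention assessment moments".

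The Data analysis section also applies intention-to-treat to every Study III analysis, with all randomised participants included, and fills missing data by last observation carried forward (LOCF). The article describes no lagged model, no reverse-direction model and no mediation model using the control group.

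**The concern.** The model class and the interpretation are both fixed in the article, and they do not match. A two-wave latent change score model supplies one change in the process and one in the outcome, over the same weeks. The path between them re-expresses how the two changes covary. Words such as impact, promote and responsible claim an order and a cause that this covariance does not carry.

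Rival explanations are realistic here. All outcome and process measures are self-report, which the Discussion concedes as a limitation, and the MPFI-24 and the GAD-7 share a two-week recall window. A participant whose way of reporting shifts during treatment would move on both scales. At stake is the mechanism conclusion, which the Discussion presents as a first for adolescents with SAD and GAD.

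**Working it through.** **1. Why fit cannot show direction.** Let dX be process change, dY outcome change, and B the two baselines. The joint density factors in two ways:

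f(dX, dY | B) = f(dX | B) · f(dY | dX, B) = f(dY | B) · f(dX | dY, B).

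When each change is regressed on both baselines, the two versions are saturated in the same covariance matrix and have the same likelihood. This holds for any single pair of waves, so it does not depend on which pair is meant.

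**2. Illustration in treated participants.** The parameters are assumed, since the article gives none. Changes have within-arm SD 1 and within-arm correlation 0.50. One million subjects were simulated, half of them treated.

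| Structure | Slope dY on dX, treated | Slope dX on dY, treated |
|---|---|---|
| PI/PF drives outcome | 0.50 | 0.50 |
| Outcome drives PI/PF | 0.50 | 0.50 |
| Common cause drives both | 0.50 | 0.50 |

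**3. What adding controls changes.** With the arm in the model, the direct arm coefficient is c − b·a. Here a is the arm effect on dX, c the arm effect on dY, and b the within-arm slope.

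- PI/PF drives outcome: a = 0.6, c = 0.3, so 0.3 − 0.5 × 0.6 = 0.00.
- Outcome drives PI/PF: a = 0.3, c = 0.6, so 0.6 − 0.5 × 0.3 = 0.45.
- Common cause, with the arm acting on both: a = 0.6, c = 0.3, so 0.3 − 0.5 × 0.6 = 0.00.

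The simulation gave 0.00, 0.45 and 0.00. In this set-up controls separate reverse direction from the hypothesis but do not separate a common cause. The separation depends on the assumed arm effects.

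**4. Numbers available.** From the Sample size section: 29 + 29 = 58 ACT participants, and 58 + 29 = 87 with controls. Lagged models can use only the 58, because controls have no follow-up. For scale, the power to detect a simple correlation of 0.3 (two-sided 5%, Fisher z) is 0.63 at n = 58, 0.56 at n = 50 (25 per group) and 0.35 at n = 29 (one group).

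**5. LOCF.** A participant lost before the post assessment gets exactly zero change on both scales. Let a fraction p be lost, and let the changes of the others be independent with mean m on each scale, in units of the SD of change. Then:

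r = p·m² / (1 + p·m²).

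With the article's 17% dropout and assumed m = 0.5, r = 0.0425/1.0425 = 0.04. With m = 1.0, r = 0.17/1.17 = 0.15. The effect is modest but favours the hypothesis. At follow-up, a carried-forward outcome equals the post outcome, which would distort a lagged regression.

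**The case against.** The strongest reply is that this is an exploratory question described in a few sentences of a journal article, with details such as the choice of waves and any reverse-path check left to a fuller plan. That is fair for the omitted detail. It does not cover the mismatch, because the two-wave model and the causal reading are both stated.

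A reader might go further in four ways that the article does not support:

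- **That controls are excluded.** The Aims and the Discussion place the question in the intervention groups, but the intention-to-treat sentence covers all Study III analyses. The text is ambiguous on this point. If controls are included, the two changes are still concurrent.
- **That no randomised test of ACT on PI/PF is planned.** PI/PF processes are secondary outcomes, and the mixed ANOVAs compare groups including control. Only the joint mediation model is missing.
- **That a shared time trend would mimic a mechanism.** A uniform trend goes into the mean change and adds nothing to the covariance of individual changes. Only shared change that differs between persons is a threat.
- **That a positive result is guaranteed.** Both means can move with no correlation between individual changes, and significance is not assured at these numbers.

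Two technical replies also stand in part. Equal likelihood holds for the saturated form. Equality constraints across SAD and GAD could make the two versions fit differently, but that would reflect the constraint and not time order. The remedies are also limited: the model with controls keeps the simultaneity, and the lagged models are unrandomised and study the period after therapy.

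**Conclusion.** The concern holds in this limited form. The planned model estimates an association between concurrent changes, and the article reads it as process change driving outcome change. Direction and person-level common causes cannot be separated over one pair of waves. The 0.50 slope is illustrative; the identification result does not depend on its size, but it does assume the saturated form with both baselines as predictors. Whether controls enter these models is unclear and needs one sentence.

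This is an improvement that should be made. It is not a flaw in the trial's efficacy comparison, which does not rest on these models. Choosing the two MPFI-24 composites for a confirmatory test, with the 12 subscales as exploratory, is an option and not part of the error.

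**What to change.** 1. Report the two-wave result as an association between concurrent changes. Align the wording of the Aims, Data analysis and Discussion sections with that.
2. State that randomised controls enter the pre-post model. Specify arm to PI/PF change to post outcome, adjusted for baseline process, baseline outcome and diagnosis. Note that this helps against reverse direction but not against a common cause.
3. In ACT participants, add lagged models of the 3- and 6-month outcome on post-intervention PI/PF, adjusted for post outcome and baseline values. Fit the reverse path (post outcome to later PI/PF) alongside.
4. Fit these models to observed data, for example by full-information maximum likelihood in Mplus, and not to LOCF values, because carried-forward scores force zero change.

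The cost is analysis work and rewording; no further data collection is needed. The downside is precision. The lagged models have at most 58 participants, fewer after dropout, and will say little if gains are stable after treatment. They are also unrandomised, so they strengthen the inference without proving it.

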### Sample size

Participants recruited in Study II will be randomly assigned to one of the three groups of Study III (cf. Figure. 1). G*Power was used to calculate sample size considering Study III requirements for repeated measures analysis with two groups (considering that the RCT groups will be compared two at a time) and 4 assessment moments. Power analysis for medium effects (f = 0.25) – chosen based on previous ACT studies with adolescents (e.g., [27–30, 60, 80]) –, with a significance level of 0.05 and power of 0.95 requires a sample size of 25 per group. To account for the expected 17% dropout rate reported in a previous meta-analysis of ACT-based interventions [81], the research team intends to collect 4 additional participants per group. Accordingly, Study II will rely on two clinical groups (i.e., SAD and GAD,n ≥ 87) of at least 44 adolescents each, and a mentally healthy group of 29 adolescents (i.e., total n for Study II ≥ 116). For Study III, the clinical participants (i.e., n ≥ 87) will be then assigned to two intervention groups of 29 adolescents each, one for SAD and one for GAD participants, or to a control group of 29 adolescents, evenly distributed between adolescents presenting with SAD or GAD diagnoses.

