
This study presents some foreseen limitations that are, nevertheless, necessary for its viability. Firstly, it focuses solely on SAD and GAD, disregarding other ADs that also present significant prevalence rates and impairments during adolescence. Additionally, the control group will not receive intervention within this project. To ensure these adolescents receive appropriate care, they will be assessed after completing the control condition and referred to school psychology services if difficulties persist. They will also be explicitly informed about the possibility of discontinuing their participation in the study to seek treatment, without any consequences. It is also important to note that the control group may not be entirely comparable to either of the intervention groups, which could lead to inherent disparities and the introduction of potential confounding variables. Based on ACT transdiagnostic premises, we believe that these differences will not significantly influence our findings. Nevertheless, the authors have devised a contingency plan to address this potential limitation, if necessary (i.e., gathering two independent control groups: one consisting solely of adolescents with SAD and another comprising only adolescents with GAD). We also acknowledge that by only using self-report measures, data collection may be susceptible to the effects of social desirability, and only a limited comprehension of the psychological constructs assessed is provided. Moreover, we anticipate dropouts to be a significant challenge in this study. To prevent its impact, the research team plans to recruit more participants than the minimum needed for each condition. This approach will allow us to account for potential attrition and ensure that sample size remains adequate throughout the study, maintaining statistical power. Efforts will be made to engage and motivate participants throughout the duration of the study to maximize retention rates (e.g., by sending thank you messages after each assessment moment). Lastly, we acknowledge that by not considering a group with comorbid GAD and SAD, we cannot fully elucidate the applicability of transdiagnostic principles to adolescents. Future research should consider comorbidity and/or cascading effects of mental health difficulties as relevant outcomes to better address the complex issues related to ACT as applied to adolescent mental health.

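### Last observation carried forward shrinks any true relapse at follow-up and can create a process-outcome association in the mechanism models where none exists

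*Protocol article*

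**What the plan says.** The Data analysis section states that "All Study III analyses will be carried out according to an intention-to-treat principle as suggested by the CONSORT guidelines", that every randomised participant is included, and that where data are missing "the last observation carried forward method will be employed". The same section lists the Study III analyses: mixed ANOVAs over the assessment moments for treatment effects, and "performing two-wave latent change score models" for mechanisms of change. Carrying forward is not named separately for the second set; it reaches them through the scope statement. No sensitivity analysis for missing data is described. The section does promise efforts to collect outcomes from participants who stop the intervention.

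Two expected results in AIMS bear on this. On stability at 3 and 6 months: "We expect improvements in the two intervention groups to be maintained". On mechanisms, similar effects are expected in both intervention groups, "with changes in PI/PF predicting changes in primary (i.e., anxiety symptoms) and secondary (i.e., flourishing) outcome variables", where PI/PF is psychological inflexibility/flexibility.

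The Sample size section uses an "expected 17% dropout rate reported in a previous meta-analysis of ACT-based interventions", and the Discussion adds that "we anticipate dropouts to be a significant challenge in this study". Controls are assessed at two time points only (Study design) and are "explicitly informed about the possibility of discontinuing their participation in the study to seek treatment" (Discussion).

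**The concern.** Carrying the last value forward assumes that nothing changes after a participant is lost, and the analysis then treats the filled value as observed. In this trial that touches two stated hypotheses.

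- **Maintenance.** For anyone lost after post, the post-to-follow-up change is entered as exactly zero, which is the value the hypothesis predicts. With no controls at 3 and 6 months, maintenance rests on change within the intervention groups, so there is no comparator to offset this.
- **Mechanism.** For anyone lost before post, both the process change and the outcome change are entered as zero. If the others improve on both, a cluster at (0, 0) beside a cluster at (improved, improved) looks like an association, even when the two changes are unrelated within persons.

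At stake are the size of the reported maintenance and the credibility of the mechanism finding, which the Discussion presents as the first of its kind.

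**Working it through.** **Inputs from the protocol article.** Dropout 17%; 29 per intervention group, so 58 in the two groups together; f = 0.25, alpha 0.05, power 0.95, two groups, four assessments (Sample size).

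**The plan's own figure.** The article gives no figure for the effect of carrying forward. Its 25 per group reproduces from the noncentral F for the group-by-time interaction, lambda = f²·N·m/(1 − rho) with N = 50 and m = 4, if the correlation between assessments is 0.3 (not stated, so assumed) and sphericity holds. At 17%, 58 × 0.17 = 9.9, so about 10 intervention participants are lost.

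**Assumptions.** The size of the mean changes, the size of any relapse, and when participants are lost are not in the article.

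**1. Maintenance: lost after post.** Let d be the true mean relapse, L the mean relapse in those lost, and p the share lost. Carrying forward replaces L by 0, so the estimate is d − p·L.

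- Lost at random, L = d = 0.40 SD: 0.40 × (1 − 0.17) = 0.33 SD. At p = 0.30, used only as a range, 0.28 SD.
- Loss related to relapse: one simulated scenario gave about 0.15 SD at 17%. This implies L = (0.40 − 0.15)/0.17 ≈ 1.5 SD.

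Detection under random loss, n = 58, SD of change 1 (wave correlation 0.5):

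- Carried forward, the variance of change is (1 − p)(1 + p·d²), so the expected test statistic is about d·√[(1 − p)n]/√(1 + p·d²) = 0.40 × √48.14/√1.027 = 2.74.
- Observed data only: 0.40 × √48.14 = 2.78.
- Simulated detection is 78% for both, against about 86% with complete data. At 30% missing it is about 70% for both.

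The loss of power therefore comes from the missing data. What carrying forward adds is the shrunken estimate.

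**2. Mechanism: lost before post.** Score both changes so that the expected direction is positive, in SDs of change, with mean m and true correlation rho in those observed. A share p sits at (0, 0). Then

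covariance = (1 − p)·rho + p(1 − p)m², variance = (1 − p) + p(1 − p)m²,

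so r = (rho + p·m²)/(1 + p·m²). With rho = 0:

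| Share lost before post | Mean change m | p·m² | Induced r | False positives, n = 58 | n = 29 |
|---|---|---|---|---|---|
| 17% | 0.5 | 0.0425 | 0.04 | about 8% | 6–7% |
| 17% | 0.8 | 0.109 | 0.10 | about 13% | 9–10% |
| 17% | 1.0 | 0.17 | 0.145 | about 21% | 13–14% |
| 17% | 1.2 | 0.245 | 0.20 | about 33% | about 19% |
| 8.5% (half) | 1.0 | 0.085 | 0.08 | about 10% | about 8% |

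The false-positive rates are simulated at a nominal 5%. Observed data with random dropout gave 4% to 6%. If m = 0 there is no induced correlation. A true correlation of 0.40 at m = 1.0 becomes (0.40 + 0.17)/1.17 = 0.49. The test is a simple correlation; covariates in the planned models are not stated.

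**3. Pre-post comparison with control.** Carrying baseline forward in an intervention group replaces the expected improvement by zero and dilutes the effect. In controls, it hides whatever change would have occurred in either direction.

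**The case against.** A reader might infer three stronger things, and the article supports none of them.

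- **That the maintenance result is guaranteed.** It is not. Only the missing share is set to zero, and under random loss the test detects a 0.40 SD relapse as often as an observed-data analysis does. Loss related to relapse also biases the observed mean: in the 0.15 SD scenario it would be 0.15/0.83 ≈ 0.18 SD, still far below 0.40.
- **That both distortions occur at full size.** The article gives a single 17%. A participant lost before post feeds the mechanism artefact, and one lost after post feeds the shrinkage. The 17% is also a dropout rate from earlier ACT-based interventions, and because outcomes are to be sought after the intervention is stopped, the share with missing outcomes may be smaller.
- **That efficacy against control is biased in favour of treatment.** Dilution in the intervention groups works the other way. Controls may leave to seek treatment, but the article does not say that those who worsen will do so. If they did, freezing them at baseline would make the control group look better.

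The mechanism artefact also depends on mean change. If the planning value f = 0.25 is read as roughly 0.5 SD (2 × 0.25, an assumption; change within a treated group could be larger), it is small: r = 0.04.

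These points limit the size of the problem. They do not defend the method: the follow-up estimate stays biased towards no relapse, and the false-positive rate of the mechanism test depends on how much the participants improve.

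**Conclusion.** The concern holds in limited form. The article itself fixes carrying forward as the only missing-data method for Study III, so this is a stated choice and not a detail left to an analysis plan.

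- **Follow-up:** true relapse is understated by the share lost times the mean relapse in those lost, which is 0.40 to 0.33 SD at 17% lost at random after post, and more if loss is related to relapse. The estimate is biased; detection is no lower than with observed data.
- **Mechanism:** a spurious association in the hypothesised direction, from negligible to serious. With all 17% lost before post, r runs from 0.04 to 0.20 and false positives from about 8% to 33% at n = 58. With half lost before post and mean changes of 1.0 SD, r is about 0.08 and the rate about 10%.
- **Pre-post efficacy:** no established sign, and possibly conservative.

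The first two are alternatives and must not be added. Both rest on assumed mean changes, relapse size and timing of loss.

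**What to change.** Replace carrying forward with the following, settled before outcome data are seen:

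1. **Treatment effects.** Use a likelihood-based repeated-measures mixed model (SPSS MIXED) on all observed assessments of all randomised participants. Include baseline as one of the response occasions and not also as a covariate. Include group, time, group by time, and diagnosis where estimable.
2. **Contrasts.** Compare with control at post only. Make the 3- and 6-month comparisons within and between the intervention groups, because controls have two assessments and no control contrast can be estimated later.
3. **Mechanism models.** Use full-information maximum likelihood in Mplus.
4. **Sensitivity.** Add one analysis in which participants with missing outcomes do worse than the model predicts, since likelihood methods too are biased when loss depends on unobserved relapse.

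All randomised participants stay in the analysis, so the intention-to-treat aim is kept. The article already names SPSS and Mplus, and no extra participants, visits or measures are needed. The cost is a change of primary model from the mixed ANOVA and slightly more analysis work.
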